### Individually targeted coaching component

The coaching is based upon Motivational Interviewing [22] and is also inspired by other theories such Social cognitive theory [23] and the behavioral model "Transtheoretical model of Change" by Prochaska and DiClemente [24]. The coaching is delivered by a trained coach (dietitian, physiotherapist or a nurse) four times the first year and twice a year thereafter. The coach makes an appointment with the family on a time that fits the family. The coaching takes place in the family's home, or if requested, at the clinic. Each coaching session is planned to take around one and a half hour the first visit and one hour the other session. The coaching includes goal setting, report of the current situation, identifying problems, assisting in problem solving; and providing positive encouragement for further development. If the family wishes additional advice between the coaching sessions, they are contacted via telephone and mails, all contacts are documented and stored in the family's files. These ways of communication could provide regular contact with a greater number of families.

### Control group

The control group families receive usual care from their CHCC nurse. In addition, these families will get a general health newsletter at baseline and are thanked yearly with gifts (to a maximum value of €20.00) after completed questionnaires.

### Reference group

The reference group of children with lean parents will receive usual care from their CHCC nurse and are thanked yearly with gifts (to a maximum value of €20.00) after completed questionnaires.

The Regional Ethical Review Board in Stockholm County has reviewed and approved the protocol dnr 2009/217-31.The protocol for this study is registered with the clinical trials registry (clinicaltrials.gov, ID: ES-2010)

## Intervention fidelity and data warehouse

### Quality control

To assure the quality of intervention delivery, all Early STOPP workers, who recruit and administer the baseline questionnaire, have initial training in how to explain the study, how to take consent and how to administer the questionnaire. Personal coaches receive standardized training. A coach's manual contains detailed information specific to each group including the educational material, timing of each session, suggestions and tips to the families. Coaches attend a weekly meeting with the project manager to ensure the protocol adherence. Everyone taking anthropometric measurements, including project workers and clinical nurses is trained in the appropriate technique how to check, calibrate and maintain the necessary equipment. Audio and videotaping of intervention sessions is conducted to assess fidelity of delivery using standardized forms. Using these, the coaching and feedback is provided to the coaches to optimize the intervention delivery.

### Data handling

All data collected according to the agreed Standard Operating Procedures (SOPs) is given a unique study identifier and stored in a data warehouse. This includes data from the clinical analysis of blood samples, data from the baseline questionnaires, and routine clinical data (Table 1). All deviations from the SOPs, such as temperature changes or freeze/thaw episodes, and equipment failures, are recorded. Review of all storage equipment will be done annually. Quality control and maintenance of the data warehouse is the responsibility of the PIs and is controlled by the strict rules of the Biobank laws at Karolinska Institutet.

**Table 1 T1:** Study measures and timing.

	Age (Years)					
	
	1	2	3	4	5	6
**Anthropometry**						
BMI/Waist (C+P)	X	X	X	X	X	X
Blood pressure (C+P)	X	X	X	X	X	X
						
**Biomarkers**						
Blood (C+P)	X		X			X
Feces (C)	X	X	X	X	X	X
Saliva (C+P)	X	X	X	X	X	X
						
**Diet**						
Survey (C+P)	X	X	X	X	X	X
Diary (C+P)	X	X	X	X	X	X
						
**Physical Activity**						
Survey (C)	X	X	X	X	X	X
Accelerometer (C+P)	X	X	X	X	X	X
Hempel Assessment (C)		X		X		X
						
**Sleep**						
Survey (C+P)		X		X		X
Diary (C+P)		X		X		X
Accelerometer (C+P)		X		X		X
						
**Stress**						
Survey (P)		X	X			X

C = Child, P = Parents

## Measures

Primary and secondary outcomes are measured as detailed below.

### Primary and secondary outcomes

Primary outcome is BMI sds-score and the secondary outcomes are PA, sedentary behaviour, motor function/development, sleeping habits, food intake, eating patterns and quality of life. These outcomes require repeated collection due to the rapid changes in height, weight, eating, motor development and PA behaviours in infants. They will therefore be measured at baseline (1 year of age) and yearly thereafter. For children in the intervention group, height, weight and waist circumference are measured every 6 month. Metabolic profile indicators, secondary outcomes, as reflected in biomarkers will be collected at the age of 1, 3 and 6.

Data on demography and socio-economic status is collected by self-report. Parent and infant data is collected by parental/carer self-completed questionnaires and objective measures (Table 1). The questionnaires include already existing validated questionnaires as well as additional questions developed by the Early STOPP project team for topics not reflected in the existing questionnaires. The questionnaires are completed by each parent separately at home before the annual visit. Together these questionnaires take between 30-45 minutes to complete.

### Anthropometry and blood pressure

Trained staff members, using standard procedures and calibrated instruments, collect height, weight and waist-circumference on the infant and parents. Weight is measured with portable scales (Tanita HD-316, Tanita Corp.; Tokyo, Japan) to the nearest 0.1 kg, with shoes and heavy clothing removed. Height is measured to the nearest 0.1 cm using a fixed stadiometer. Based upon height and weight BMI is calculated. Waist circumference is measured right between the lower costal (rib) border and the iliac crest using a nonextensible tape. BMI and waist circumference sds-score will be calculated based upon age- and sex-specific reference values [25,26]. Systolic and diastolic blood pressure (BP) are measured using an automated BP monitor (Dinamap model 8101, Critikon Inc.; Florida, USA) under standard conditions [27]. All of these measurements take place in a private room.

### Dietary intake and eating behaviour

A four-day estimated food diary, covering two weekdays and two weekend days, will assess the children's dietary intake. This diet assessment method is chosen since both qualitative and quantitative aspects of the children's diet intake will be evaluated [28]. The parents' diet quality will be assessed using a semi-quantitative food frequency questionnaire (FFQ) developed and validated by the Swedish National Food Administration. To measure children's eating habits; the Children's Eating Behaviour Questionnaire (CEBQ) will be used [29]. The CEBQ is a multi-dimensional, parent-report questionnaire aims to provide a useful measure of eating styles to study the early precursors of obesity and eating disorders. The CEBQ consists of 35 statements originally derived from interviews with parents about their children's eating behaviour and the literature on the subject. Originally the items covered eight dimensions (factors) of eating style: Food Responsiveness (FR), Emotional Over-Eating (EOE), Enjoyment of Food (EF), Desire to Drink (DD), Satiety Responsiveness (SR), Slowness in Eating (SE), Emotional Under-Eating (EUE) and Food Fussiness (FF).

Outcome measures from the food diary, FFQ and CEBQ will be energy and nutrient intake, meal patterns, times and quantity of vegetable and fruit intake as well snacking patterns.

### Physical Activity, sedentary behaviour and motor function

Parents will report the frequency and duration in health related PA and sedentary behaviour during the previous week using the International Physical Activity Questionnaire (IPAQ), long version [30] at baseline. This is done to be able to compare with national PA data. When the children are 2, 3, 4, 5 and 6 years of age the parents will answer a question about their leisure time PA in the past 12 months [31]. This is done to get a crude measure of the parent's PA levels over a year. Further, the parents will also report the number of hours their child typically spends playing outdoors on weekdays and weekend days. In addition, every year, parents and the child's PA and sedentary behaviour will be assessed objectively using the ActiGraph GT3X+ accelerometer (ActiGraph, LLC, Fort Walton Beach, FL). The ActiGraph has shown high agreement with energy expenditure and measures of time spent in different intensities for adults as well as for children 3 year and up [32-34]. A calibration study on children 2 years of age will be performed within the Early STOPP project. Outcome measures from the accelerometer will be total PA expressed as counts per minute, time spent in different intensities of PA as well as sedentary time. The families will get verbal and easy to read instructions from the research staff on how to wear the accelerometer (around the non-dominant wrist using an elasticated belt). The participants are asked to wear the accelerometer for seven consecutive days, but for the analysis we will include participants that have at least four days of measurements [35].

Motor function of the children will be assessed using the technique described by Hempel [36]. The assessment is age specific and will take place when children are 2 and 4 years of age, respectively. The assessment takes about 30 minutes and will be videotaped to enable analysis afterwards. The examination focuses on motor-functions such as prehension, sitting, crawling, standing and walking behaviours, in a standardized free-field situation. The examination is based mainly on observation of spontaneous motor behaviour since observation is a suitable tool for assessment of qualitative aspects of motor function. The assessment results in three outcome measures; a fluency score, mainly considering fluency of movements (range 0-13); a Clinical classification with four categories ranging from normal to abnormal; a Neurological Optimality Score (range 0-58) [37]. The inter-rater reliability of the Hempel assessment is satisfactory [38].

### Sleeping habits

Assessment of children's and parents' day-to-day sleep pattern for weekdays and weekend at age 2 will be conducted and the ActiGraph GT3X+ accelerometer will be used. The ActiGraph provides an objective recording of sleep duration, sleep efficiency and sleep timing, and is a reasonable tool to evaluate how sleep varies on a day-to-day basis. ActiGraph has shown a good reliability compared with polysomnographic measures of sleep in adults [39,40] and young persons [40,41]. It is possible that the accelerometer does not discriminate entirely between sleep and motionless wakefulness, for example watching TV, which is why sleep diaries are preferred as a complement. For this purpose parents will be asked to complete the brief Infant Sleep Questionnaire (BISQ) [42] to assess children's sleep on a daily basis (7 days). The BISQ has been validated against accelerometry and daily-logs and its sensitivity in documenting expected developmental trends in young children's sleep and the effects of environmental factors have been established [42]. Outcome measures are sleep duration and sleep efficiency (time in bed/sleep time), and settling times. Parents sleep pattern and sleep behaviour will be assessed with the Karolinska sleep/wake diary [43] and parents habitual sleep quality will be assessed with the Karolinska Sleep Quality Index (SQI) [44]. The SQI has been validated against polysomnography and show good correlations with objective sleep parameters [45]. Parenting stress will be assessed by Parenting Stress Index (PSI) [46], the Swedish version.

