### Hypothesis

In comparison to the control group, during the course of intervention, children in the intervention group families are expected: to have reduced BMI gain, to consume more fruits and vegetables and less unhealthy foods such as soft-drinks and energy-dense snack foods, to spent more time being physically active and less time sedentary, specifically TV viewing and computer games, to sleep independently and have healthy sleep habits.

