## Planned data analysis

To achieve a normal distribution the variables will be transformed if needed or non-parametric statistics will be used. Analysis of covariance will be used to test for differences in baseline characteristics between the study arm and adjustment will be made to analyses as required. An estimation of intervention effect on outcome measures will assessed at each follow-up observation (every year post-baseline) on an intention to treat basis. A mixed model will be used to test the average effect of the intervention after taking account of baseline covariates.

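### Sleep efficiency is defined as the reciprocal of efficiency (time in bed over sleep time), so the printed ratio rises as sleep gets worse

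*Protocol article*

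**What the plan says.** The Sleeping habits section of the protocol article names the sleep outcomes and gives a formula for one of them: "Outcome measures are sleep duration and sleep efficiency (time in bed/sleep time), and settling times". No other definition of sleep efficiency appears in the article. Earlier in the same section the device is described this way: "The ActiGraph provides an objective recording of sleep duration, sleep efficiency and sleep timing". No second formula accompanies that statement.

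Under Primary and secondary outcomes, sleep has secondary status: "the secondary outcomes are PA, sedentary behaviour, motor function/development, sleeping habits, food intake, eating patterns and quality of life". The Hypothesis section expects children in the intervention group "to sleep independently and have healthy sleep habits". Under Planned data analysis the general rule is: "An estimation of intervention effect on outcome measures will assessed at each follow-up observation". That section also allows for transforming variables or for using non-parametric methods.

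**The concern.** An efficiency measure is the useful part divided by the whole. For sleep, this is time asleep divided by time in bed. The article prints the two the other way round. The text is intact prose, and it is a positive definition of a named outcome, so this is not a detail left to a fuller document.

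Sleep is one of the behaviours the programme targets, and the hypothesis expects better sleep in the intervention group. An outcome labelled efficiency that goes up when a child sleeps less of the time in bed conflicts with its own label. Anyone who derived it by hand from the printed ratio would report a quantity whose direction and scale differ from what the name leads a reader to expect.

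**Working it through.** **Inputs.** The formula comes from the Sleeping habits section. The article gives no hours in bed or asleep, so the hours below are illustrative assumptions. There is no stated figure to reproduce.

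Let B = time in bed and S = sleep time, with sleep counted within the time in bed, so S ≤ B.

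- As printed: R = B / S.
- Usual meaning: E = S / B, so R = 1 / E.

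**Bounds.** Since S ≤ B, E is at most 1 and R is at least 1. R equals 1 only when no time in bed is spent awake. For fixed B, R rises as S falls.

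**Illustration with B = 10.5 h**

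- S = 9.5 h: R = 10.5/9.5 = 1.105; E = 9.5/10.5 = 0.905, or 90%.
- S = 9.0 h: R = 10.5/9.0 = 1.167; E = 9.0/10.5 = 0.857, or 86%.

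Losing half an hour of sleep changes R by 1.167 − 1.105 = +0.06 and E by 0.857 − 0.905 = −0.048, about 5 percentage points. The directions are opposite.

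**Illustration with B = 11 h**

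| S (h) | R = B/S (as printed) | E = S/B |
|---|---|---|
| 11 | 1.000 | 1.000 |
| 10.5 | 1.048 | 0.955 |
| 10 | 1.100 | 0.909 |
| 9 | 1.222 | 0.818 |
| 8 | 1.375 | 0.727 |

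The scale differs as well as the direction. Going from 10 to 9 h and then from 9 to 8 h lowers E by 0.091 each time. The same steps raise R by 0.122 and then by 0.153.

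**Does the sign of a difference in means always reverse?** No. Suppose arm A has efficiencies 0.50 and 1.00, and arm B has 0.74 and 0.74.

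- Mean E: A = 0.75, B = 0.74.
- Mean R: A = (2.00 + 1.00)/2 = 1.50; B = 1/0.74 = 1.35.

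Arm A is higher on both scales. Order reverses for any two single values, but for means only generally. A mean of reciprocals is not the reciprocal of the mean, so a result on the printed scale cannot be converted back from the group means alone.

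**What if naps count as sleep?** If S includes sleep outside the time in bed, the bound fails. With B = 10.5 h and total sleep of 11 h, R = 10.5/11 = 0.955 and E = 11/10.5 = 1.048, an efficiency above 100%. Swapping the terms is therefore not quite enough: numerator and denominator must cover the same sleep period.

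**The case against.** The strongest reply is that this is a slip of wording with no effect on the analysis. The section presents sleep efficiency as something the accelerometer records, and nothing shows that staff will calculate the bracketed ratio by hand. The slash might even be read as listing two components. The reply about the device is fair and makes a slip the likelier explanation. The list reading is weak, because brackets directly after the name of a ratio measure read as its formula. Neither reply makes the printed definition correct. If the device value follows the usual definition, the article's formula does not describe its own data.

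A reader might also draw stronger conclusions, which the article does not support:

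- That every between-arm difference changes sign. The two-arm example above shows that it need not.
- That the ratio always exceeds 1. It equals 1 when no time in bed is spent awake, and it can fall below 1 if naps are counted.
- That extreme nights would dominate the mean. The illustrative range reaches only 1.375, and the analysis section already allows transformation or non-parametric methods.
- That a benefit would be reported as harm. This requires analysts to use the printed ratio and then interpret it by its usual label. Nothing in the article shows that either will happen.
- That the formula governs the parents' data too. The sentence follows the description of the child sleep questionnaire and precedes the parents' instruments, so its reach to parents is unclear.

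**Conclusion.** The definition is wrong as written: it is the reciprocal of efficiency, and nothing else in the article corrects it. With sleep counted within time in bed, the printed ratio is at least 1 and rises as an individual's sleep worsens. If it were computed as printed, between-arm differences would generally have the opposite direction and a different scale, and would not match the usual meaning of the term. The consequence is conditional on that computation, and the hours used to show its size are assumptions.

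The scope is narrow. Efficiency is one of three sleep measures in the quoted sentence, within one of several secondary outcomes, and the hypothesis on sleep does not name it. The BMI-sds primary outcome, the sample size and data collection are unaffected.

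**What to change.** In the Sleeping habits section, define sleep efficiency = sleep time / time in bed (× 100%). Apply this wherever efficiency is derived, whether from the accelerometer or from diaries. State that numerator and denominator refer to the same sleep period, so that sleep outside the recorded time in bed does not enter one and not the other. If the device's own value is to be used, confirm that it follows this definition.

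The cost is a one-line edit. It needs no new data. Where the printed ratio has already been calculated, the corrected value can be obtained record by record by dividing the two recorded times the other way round.

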### Metabolic biomarkers

Fasting blood sample (50 ml for parents and 12 ml for child) is collected by a trained nurse from both parents and the child. The blood sample is analysed for inflammatory markers, cholesterol (total, HDL & LDL), triglycerides, insulin, glucose and hormones (leptin, ghrelin, adiponektin) using standard automated techniques at the KI laboratory. Parents are asked to provide a saliva sample at baseline and at follow-up at 3 and 6 years visits and stored in biobank, this will be used as a source of genomic DNA. Further, nitrate/nitrite levels will be measured in saliva and blood samples and correlated with blood pressure in both parents and their children. Saliva samples will be collected at the same time in tubes containing EDTA, with final concentration of 2 mM and stored at -80°C for later nitrate and nitrite determination. Samples will be analyzed by ion chromatography (ENO 20 Analyzer; Eicom, Kyoto, Japan). To assess the faecal bacterial flora, the microbiological samples will be taken from the stool and analyzed by using a highly parallel 454 Life Sciences GS20 pyrosequencer [47-49].

## Planned data analysis

To achieve a normal distribution the variables will be transformed if needed or non-parametric statistics will be used. Analysis of covariance will be used to test for differences in baseline characteristics between the study arm and adjustment will be made to analyses as required. An estimation of intervention effect on outcome measures will assessed at each follow-up observation (every year post-baseline) on an intention to treat basis. A mixed model will be used to test the average effect of the intervention after taking account of baseline covariates.

## Time plan for the Early STOPP RCT

The study aims to recruit 250 families. Recruitment began in winter 2010 and by Autumn 2011 it is anticipated that all participants will have completed the baseline measurements. The study will continue until children are 6 years of age. It is anticipated that protocols for each phase of follow up of participants in this study will be further adjusted.

## Discussion

To our knowledge, the current study is the first RCT of an early, family-based, lifestyle program for families "at risk" (overweight and obese parents) that will evaluate the effectiveness as well as the sustainability of an individual coaching (i.e. via personal contacts, telephone, and/or electronic mail (email) over a five-year period.

Early years of life is a time in which obesity prevention may be most effective. To our knowledge this will be the first longitudinal randomized trial to demonstrate if an early individually adapted health promotion program delivered to overweight or obese parents promotes healthy eating, PA and balanced sleeping habits. If proven to be effective, Early STOPP may protect children from the development of obesity and associated socio-economic costs.
